## 20.5 Identifiable information might be disclosed as part of study activities:

☐ Yes ☒ No

If **yes**, indicate to whom identifiable information may be disclosed:

- ☐ The subject's medical record
- ☐ The study sponsor
- ☐ Collaborators
- ☐ The US Food & Drug Administration (FDA)
- ☐ Others (specify below)
- ☐ A Foreign Country or Countries (specify below)

If **Others**, specify:

## 20.6 Indicate how data are kept secure and protected from improper use and disclosure (check all that apply): NOTE: Whenever possible, do not store subject identifiers on laptops, PDAs, or other portable devices. If you collect subject identifiers on portable devices, you MUST encrypt the devices.

- ☒ Data are stored securely in My Research
- ☒ Data are coded; data key is destroyed at end of study
- ☒ Data are coded; data key is kept separately and securely
- ☒ Data are kept in a locked file cabinet
- ☒ Data are kept in a locked office or suite
- ☒ Electronic data are protected with a password
- ☒ Data are stored on a secure network
- ☒ Data are collected/stored using REDCap or REDCap Survey
- ☐ Data are securely stored in OnCore

## 20.7 Additional measures to assure confidentiality and protect identifiers from improper use and disclosure, if any:

PHI on pediatric patients obtained from electronic health records and from ZSFG HA surveys (not study-related) will be kept on an encrypted, password-protected laptop with password-protected files in MyResearch. Data analyses will be based on data from research surveys and health records data and also kept in MyResearch files. Biomarker data will be sent only accompanied by Study Enrollment number without other identifiers.

## 20.8 This study may collect information that State or Federal law requires to be reported to other officials or ethically requires action:

☒ Yes ☐ No

Explain:

While we do not directly ask the suicidality question from the PHQ-9, any cases where the participants report suicidality the research assistant will immediately notify the attending physician on duty in the Pediatric Urgent Care Center.

## 20.9 This study will be issued a Certificate of Confidentiality:

☐ Yes ☒ No

## 21.0 Subjects

### 21.1 Check all types of subjects that may be enrolled:

- ☐ Inpatients
- ☒ Outpatients
- ☐ Healthy volunteers
- ☐ Staff of UCSF or affiliated institutions

### 21.2 Additional vulnerable populations:

- ☒ Children
- ☐ Subjects unable to consent for themselves
- ☐ Subjects unable to consent for themselves (emergency setting)
- ☐ Subjects with diminished capacity to consent
- ☒ Subjects unable to read, speak or understand English
- ☐ Pregnant women
- ☐ Fetuses
- ☐ Neonates
- ☐ Prisoners
- ☒ Economically or educationally disadvantaged persons
- ☐ Investigators' staff
- ☐ Students

Explain why it is appropriate to include the types of subjects checked above in this particular study:

We are conducting this study with caregivers of patients in the ZSFG Peds Urgent Care Clinic, where many caregivers are unable to read/write English, and many are socioeconomically disadvantaged. Since the aim of the study is to document the impact of better connect patients who need resources with available community services, it is essential to recruit these families. The study is aimed at improving pediatric health outcomes so recruiting from pediatric populations is an additional requirement. We have checked the "children" box because we are accessing medical records of the index child (child receiving care at ZSFG on day of enrollment) at 12 months following enrollment.

Describe the additional safeguards that have been included in the study to protect the rights and welfare of these subjects and minimize coercion or undue influence:

We are consenting caregivers who are parents or legal guardians who have knowledge of the pediatric patients' living environment. This should minimize risks to the rights and welfare of pediatric patients. We are adding an adolescent assent requirement for using EMR utilization data at 12 months following household enrollment in the study. EMR data will be linked with study survey and biomarker data. We will obtain HIPAA authorization from all participants for whom these links will be made.

## 22.0 Inclusion of Children in Research

### 22.1 This study will enroll children who can legally consent for themselves:

☐ Yes ☒ No

If **yes**, explain why they can consent for themselves in the research setting:

If you will **ONLY** be enrolling children who can legally consent for themselves, press **SAVE and CONTINUE** to skip the rest of this section.

## 22.2 Select all the regulatory categories that apply:

- ☒ No greater than minimal risk (45 CFR 46.404, 21 CFR 50.51)
- ☐ Greater than minimal risk but presenting prospect of direct benefit (45 CFR 46.405, 21 CFR 50.52)
- ☐ Greater than minimal risk (though only a minor increase over minimal risk) and no prospect of direct benefit but likely to yield generalizable knowledge about the subjects disorder or condition (45 CFR 46.406, 21 CFR 50.53)
- ☐ Research not otherwise approvable which presents an opportunity to understand, prevent, or alleviate a serious problem affecting the health or welfare of children (45 CFR 46.407, 21 CFR 50.54)

Explain why the research in this study falls under the above category or categories:

## 22.3 Parental permission or waiver:

- ☒ Parental permission will be obtained
- ☐ Waiver of parental permission is requested: Parental permission is not a reasonable requirement
- ☐ Waiver of parental permission is requested: The waiver meets the provisions for a waiver of consent set forth in 45 CFR 46.116, Subpart A

If you are requesting a **waiver of parental permission**, explain why the study meets the regulatory criteria for this waiver:

## 22.4 Assent of children or waiver:

- ☒ Assent of children old enough to provide assent will be obtained
- ☐ Waiver of assent is requested: Children cannot be consulted or the research has prospect of direct benefit only available in the study
- ☐ Waiver of assent is requested: The waiver meets the provisions for a waiver of consent set forth in 45 CFR 46.116, Subpart A

If you are requesting a **waiver of child's assent**, explain why the study meets the regulatory criteria for this waiver:

## 22.5 Documentation of permission and assent (select all that will be used):

- ☒ Permission form addressed to the parents
- ☒ Simplified assent form addressed to the child, 7-12 years old (parents get separate form)
- ☒ Assent form addressed to the child, 13 years and older (for subjects and parents)
- ☐ Assent form addressed to the child, 13 years and older (parents get separate form)

Check one:

- ☒ One parent's signature will be obtained
- ☐ Two parents' signatures will be obtained

If this study is approvable under .404 or .405 and you plan to get permission from only one parent, explain why you think one parent's permission is sufficient:

The study poses minimal risk to children and caregivers.

## 22.6 This study may enroll wards of the state:

☐ Yes ☒ No

## 23.0 Inclusion of Non-English Speaking Subjects

### 23.1 Indicate which method(s) you will use to consent non-English speaking subjects:

- ☒ Preferred Method—Consent form and other study documents will be available in the subject's primary language. Personnel able to discuss participation in the patient's language will be present for the consent process.
- ☐ Short-Form—A qualified interpreter will translate the consent form verbally, and subjects will be given the Experimental Subject's Bill of Rights in their primary language, following instructions in Those Who do not Read, Speak or Understand English for required witnessing and signatures.

### 23.2 Explain how you will maintain the ability to communicate with non-English speakers throughout their participation in the study:

We plan to have a fully bilingual, bicultural trained research assistant available during study hours to communicate with Spanish-speaking participants. The consent document will be available in English and in Spanish. Interpreter services will not be used to consent patients for this study.

## 24.0 Recruitment

### 24.1 \* Methods (check all that apply):

- ☒ Study investigators (and/or affiliated nurses or staff) recruit their own patients directly in person or by phone.
- ☐ Study investigators recruit their own patients by letter. Attach the letter for review.
- ☐ Study investigators send a "Dear Doctor" letter to colleagues asking for referrals of eligible patients. If interested, the patient will contact the PI or the PI may directly recruit the patients (with documented permission from the patient). Investigators may give the referring physicians a study information sheet for the patients.
- ☐ Study investigators provide their colleagues with a "Dear Patient" letter describing the study. This letter can be signed by the treating physicians and would inform the patients how to contact the study investigators. The study investigators may not have access to patient names and addresses for mailing.
- ☐ Advertisements, notices, and/or media used to recruit subjects. Interested subjects initiate contact with study investigators. Attach ads, notices, or media text for review. In section below, please explain where ads will be posted.
- ☐ Study investigators identify prospective subjects through chart review. (Study investigators request a Waiver of Authorization for recruitment purposes.)
- ☐ Large-scale epidemiological studies and/or population-based studies: Prospective subjects are identified through a registry or medical records and contacted by someone other than their personal physician. (Study investigators request a Waiver of Authorization for recruitment purposes.)
- ☐ Direct contact of potential subjects who have previously given consent to be contacted for participation in research. Clinic or program develops a CHR-approved recruitment protocol that asks patients if they agree to be contacted for research (a recruitment database) or consent for future contact was documented using the consent form for another CHR-approved study.
- ☐ Study investigators list the study on the School of Medicine list of UCSF Clinical Trials website or a similarly managed site. Interested subjects initiate contact with investigators.
- ☐ Study investigators recruit potential subjects who are unknown to them through methods such as snowball sampling, direct approach, use of social networks, and random digit dialing.
- ☐ Other

If **Other**, explain:

### 24.2 \* How, when, and by whom eligibility will be determined:

A designated research study assistant located in pediatric urgent care will introduce study and determine initial eligibility based on language and patient age. Once family has expressed interest in the study, the research assistant will ensure family members meet all eligibility requirements by asking questions related to inclusion/exclusion criteria.

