The San Francisco General Hospital (SFGH) Health Advocacy (HA) intervention specifically includes implementing a navigation desk at the SFGH pediatric urgent care center. The program is available to all families presenting for care to the SFGH Primary Care Clinic. All families entering the site are offered screening for social issues affecting their health, including nutrition, housing and financial insecurity. Families with a positive screen are referred to the HA program, where navigators assist them to address each family's specific needs. Using a client management database, HA navigators follow the family over time to ensure that identified needs have been successfully addressed. The initial RCT data collection effort of the HA intervention was very successful. Results showed that participants in the intervention arm decreased needs and improved child health significantly more than the control group arm (publication pending). In this new study phase, we plan to examine the effects of the HA program on a more robust set of survey data including detailed measures of caregiver and child health and non-invasive biological data. We will collect survey responses to a broader range of health outcomes for children and their caregivers, including intermediate health outcomes like caregiver depression, work and school attendance, and biomarkers of stress IL-6/ inflammatory cytokines (oral swab collection) and hair cortisol. This work is based on existing studies showing that hair cortisol and inflammatory cytokines are important markers of socioeconomic status and social stressors.(20-23)

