#### 14.7 Exclusion criteria:

- Non-English or non-Spanish speaking parent or legal gaurdian
- Parent or legal guardian under age 18
- Parent or legal guardian accompanying patient is not familiar with the child's living situation
- Currently receiving services from the Health Advocate program or have received Health Advocate services in the past six months
- Non-San Francisco resident
- Foster child or child in clinic for a child protective clearance exam
- In clinic for exam related to child abuse
- Clinic staff

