## 16.0 Procedures

**16.1 \* Procedures/Methods (Help Text updated 9/13) For clinical research list all study procedures, test and treatments required for this study, including when and how often they will be performed. If there are no clinical procedures, describe the Methods:**

All patients in ZSFG Peds Urgent Care during study hours meeting inclusion criteria will be asked by a designated study research assistant accompanied by a study designated trained SFGH Health Advocate Research Assistant (HARA) if they are interested in the study. (See Introduction Script attached.) If there is time in the urgent care private patient room (where there are often long waiting periods for providers), the research assistant will review consents and HIPAA authorization forms with family. Otherwise, following the clinic visit, the study research assistant will escort interested patient families to the ZSFG Health Advocate office on ZSFG 6A (on the same floor and down the hall from the urgent care clinic) for eligibility review and consent process. The study research assistant will assign eligible participants a study ID#, which will be stored in a password protected REDCap file on the study's encrypted and password-protected laptop.

The Research Assistant will review consent with eligible caregivers and patients old enough to participate in consent process. Consent will include documenting study ID, completing caregiver name and contact information and child MR#. (NB: Any duplicate MRN will not be eligible for participation.) One consent form will be used for participants randomized into the intervention arm or the control arm of the study (See attached).

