Consenting caregivers will be given a copy of the study consent forms. They will also be asked to review and sign a HIPAA authorization form to enable access to separate ZSFG HA surveys/follow up and other health care records. In addition to caregiver consent, children 7 and older also will complete assent forms. (See attached study assent forms.) With caregiver permission, children will be offered entertainment activities including bubbles and age appropriate books, games, and videos. Before caregivers complete health surveys with the Research Assistant and HARA, children 2 yo and over and all caregivers will be given a cup of water and asked to swoosh mouths with water and then swallow water. This needs to be completed 20 minutes before saliva and buccal mucosal cell collection. Following water swoosh, all participating caregivers will complete a baseline survey conducted by Research Assistant and HARA on REDCap using a computer tablet. (See attached documents for baseline and follow up surveys.) There is one self-completion portion of the survey, which includes the Patient Health Questionnaire (PHQ-8) and measures for social support and stress, that participants can read and complete themselves or ask for assistance on. After completing the survey, all participating caregivers and children then will have hair cortisol and oral buccal mucosal cell and saliva samples collected. Participants will then be randomized into the intervention arm or the control arm of the study.

Randomization will occur at the participant level using a stratified randomization method in the computer-based program REDCap. This stratified method will be used to ensure a balance of Spanish speaking families and English speaking families within the groups. After completing the study survey and biomarkers collection, the Research Assistant will leave participant dyads with the HARA for randomization. The HARA will randomly assign participants to either the intervention or the control group. The Research Assistant will have no knowledge of or access to participants' group assignments.

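### The exclusion for recent Health Advocate services is settled by asking the family; no check of program records is named, although the means for one are in hand before randomization

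*Protocol*

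**What the plan says.** Section 14.7 excludes families in this position: "Currently receiving services from the Health Advocate program or have received Health Advocate services in the past six months". Section 14.6 states the same rule as an inclusion criterion. Section 24.2 gives one method for all criteria: "the research assistant will ensure family members meet all eligibility requirements by asking questions related to inclusion/exclusion criteria".

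Other sections bear on whether more could be done:

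- **Program records exist.** Section 13.1: "Using a client management database, HA navigators follow the family over time to ensure that identified needs have been successfully addressed". It does not say how the database is indexed.
- **Prior service is plausible.** Section 13.1: "The program is available to all families presenting for care to the SFGH Primary Care Clinic". Section 11.1 calls the intervention routine in pediatric primary care. Section 14.6 admits Primary Care patients, and 16.1 expects some intervention families to be such patients.
- **Identifiers are in hand.** Section 16.1: "Consent will include documenting study ID, completing caregiver name and contact information and child MR" number.
- **Access is authorized.** Under 16.1, caregivers are asked at consent to "sign a HIPAA authorization form to enable access to separate ZSFG HA surveys/follow up and other health care records". Section 20.7 also expects patient-level data from the program's own surveys.
- **The record number has one stated eligibility use.** Section 16.1: "Any duplicate MRN will not be eligible for participation". This is not tied to earlier services.
- **Sequence.** Under 16.1, randomization follows consent, survey and samples, and is done by the Health Advocate research assistant (HARA).

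**The concern.** This criterion keeps the control arm free of the test intervention at entry. Under 16.1 a control family gets a written handout and is offered the program only after the six-month visit. The criterion asks a caregiver, during an urgent care visit, to recall a dated contact with a named program. The caregiver may not know the program by that name, may misdate the contact, or may not know of help given to another adult in the household.

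A family being served at enrollment and missed by these questions could be randomized to either arm. In the control arm it may go on receiving the intervention. In the intervention arm it may gain less, because its needs are already being worked on. Randomization spreads such families over both arms, so the expected result is a smaller between-arm difference, not an imbalance between the arms.

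**Working it through.** **Inputs from 14.4:** two-sided alpha 0.05; t-tests on change from baseline; 362 dyads per arm; 30% attrition; 253 per arm analysed; stated power of at least 80% at d = 0.25; expected effects of 0.26 to 0.43 SD for number of social needs and 0.38 to 0.46 SD for cortisol.

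**Assumption, not in the documents:** a share c of dyads contributes no contrast. No rate of prior or current service among urgent care families is given, so c = 5% and 10% are illustrations.

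**Step 1: reproduce the plan.** 362 × 0.70 = 253.4, so 253 per arm. In the normal approximation, power = Φ(d√(n/2) − 1.96). With d = 0.25 and n = 253, this is Φ(0.25 × 11.247 − 1.96) = Φ(0.852) = 0.803. The t-based value is 0.801. The stated figure reproduces, with almost no margin.

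**Step 2: dilute the effect.** The diluted effect is d(1 − c). At d = 0.25 and c = 5%, it is 0.25 × 0.95 = 0.2375. At c = 10% it is 0.25 × 0.90 = 0.225.

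**Step 3: power with 253 per arm (t-based).**

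| True effect d | c = 0 | c = 5% | c = 10% |
|---|---|---|---|
| 0.25 (stated detectable effect) | 0.801 | 0.760 | 0.714 |
| 0.26 (lowest social-needs effect) | 0.831 | 0.792 | 0.748 |
| 0.38 (lowest cortisol effect) | 0.989 | 0.982 | 0.970 |
| 0.43 (highest social-needs effect) | 0.998 | 0.996 | 0.991 |

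**Step 4: how much dilution the plan can absorb.** The smallest effect with 80% power in the normal approximation is (1.960 + 0.842) × √(2/253) = 0.249. The largest tolerable share is 1 − 0.249/d. That is about 4% at d = 0.26 and about 34% at d = 0.38. At d = 0.25 it is close to zero.

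**Step 5: is the check feasible in the stated sequence?** Section 24.4 says no protected health information is accessed before consent. A look-up after consent and authorization respects that. Under 16.1 the survey and sample collection still lie between consent and randomization, which leaves time for it.

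**The case against.** The case against has several parts, and much of it stands.

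- **Search key.** A reader might infer that the database can be searched by the child's record number. Section 13.1 names no search key and does not say that research staff can query it, so how the look-up is done must be left open.
- **Silence.** That asking is the only method rests on silence elsewhere in a short form answer. Section 16.1 also places eligibility review in the Health Advocate office when it is not done in the clinic room, and a HARA is present at approach (24.3). But no section gives that person a check, and 24.2 answers directly how eligibility is determined.
- **Model.** Zero contrast fits, at most, families being served at enrollment. A family whose services ended nearly six months before may be receiving nothing in the control arm and would get fresh navigation in the intervention arm. Current clients may also be the least likely to misreport. Applied to every ineligible family, the model would overstate the loss.
- **Effect range.** At d = 0.25 the plan has no margin, so any loss crosses 80%. At the larger effects in 14.4 the loss is minor.
- **Repair.** A reader might infer that missed families cannot be dealt with after randomization. That is too strong. Service before enrollment is a pre-randomization fact. If the records obtained under 16.1 and 20.7 cover it, it could enter as a baseline covariate or a sensitivity analysis.
- **Partial remedy.** A check at entry does not stop control families from entering the program through Primary Care during follow-up.

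None of this supplies a reason to rely on recall when program records may be consulted at little cost.

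**Conclusion.** The point holds as a modest, inexpensive improvement to enrollment. Section 24.2 has this exclusion settled by questioning, and no check of program records is named, although identifiers, authorization and a HARA are in place before randomization.

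The documents do not show that misclassification is common, and the power figures illustrate an assumed rate. If 5% or 10% of dyads contributed no contrast, power would drop from 0.80 to about 0.76 or 0.71 at d = 0.25. It would remain about 0.97 or higher at d = 0.38. The exposure therefore lies at the low end of the social-needs effect, where the sample size has little to spare. The cortisol comparison, at the effects assumed in 14.4, is hardly touched.

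**What to change.** In 24.2 and 16.1, add that after consent and HIPAA authorization, and before randomization, the HARA checks Health Advocate program records for services in the preceding six months. The search uses caregiver name and, if the database allows, the child's record number. State in the protocol which of these it supports. Keep the criterion as defined in 14.6 and 14.7, meaning services received; widening it to any contact would change eligibility, not verify it. Dyads found to have had such services are not randomized. A REDCap field recording the check must be completed before allocation can be requested.

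The cost is a look-up by staff already present, one REDCap field, and a few consented families who become screen failures before randomization. Doing the check soon after authorization would spare those families the survey and samples. The sponsor should first confirm how the database can be queried, since the time needed is not in the documents. Entry of control families into the program during follow-up is a separate matter that this check does not address.
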